## 6. Is there any additional blinding in this study?

No.

## 7. Study design

https://www.protocols.io/view/dts-tot-protocol-n92ldzn88v5b/v1

The DTS protocol consists of 4 subtasks, 2 based on the numeric value of the displayed stimuli and two based on the visual appearance of the stimuli. Within the numeric subtasks, participants are either performing the LOW/HIGH task or the EVEN/ODD task.

For the LOW/HIGH task participants have to judge, whether a single number is higher or lower than 5 and indicate their response with a keystroke. In the EVEN/ODD task participants have to decide if a stimulus (again a single number, but located spatially different) is even or odd. Again, participants are instructed to respond with a keystroke.

For the visual tasks; participants have to either perform the COLD/HOT task, where they have to decide whether the stimulus is presented in either a hot or a cold color, or they have to perform the VERTICAL/HORIZONTAL task, in which the orientation of a pattern has to be determined (see Figs 1 and 2 for an example array of stimuli for each condition, instructions can also be displayed in French).

**Fig 1 pone.0279021.g001:**
[figure not shown]
Examples of different stimuli for all subtasks of the DTS protocol.

**Fig 2 pone.0279021.g002:**
[figure not shown]
Larger example of stimuli with cue relevant for Task 3.

During the task, participants have to perform consecutive trials, where the task and stimuli will change quasi-independently from trial to trial.

For each trial, participants are presented with 3 quasi-independent pieces of information. They are presented with an instruction for the current trial in form of the task name (eg. VERTICAL/HORIZONTAL, presented 300ms before the actual stimulus) and two stimuli in form of signs or numbers. Based on the stimuli and the instruction participants are instructed to then respond as fast as possible, using either the S or the L key on a keyboard (keys were selected as they are located at a comfortable distance on the keyboard, in order to avoid straining the hands of the participants, keys will be marked with stickers for participant ease).

In total there are 96 different conditions for each trial (4 Tasks * 3 Switching conditions * 4 Congruency Conditions * 2 Response types). However, as differences in performance of individual tasks, as well as response type, are not hypothesized to have any impact on the performance of participants, 12 main conditions remain.

*Task-Switching Conditions*:

Each trial (n) is classified into one of the three Task-Switching Conditions depending on the task in trial n-1. If the task remains the same, the trial is a repeat trial. If the task switches, but remains within the same domain (LOW/HIGH to EVEN/ODD or VERTICAL/HORIZONTAL to COLD/HOT and vice versa), it is considered an internal switch trial. Finally, switches from one domain into the other (LOW/HIGH or EVEN/ODD to either VERTICAL/HORIZONTAL or COLD/HOT and vice versa) are considered external switch trials.

Note that patterns in Task 3 are not clearly visible in the document, please refer to Fig 2.

*Congruency Conditions*:

Depending on the stimuli that are presented a trial may evoke different degrees of conflict as to the correct response required. This occurs when the **task-relevant information of the stimulus** indicates, that eg. response 1 is correct, while in the presence of a non-relevant cue biasing the response in the incorrect condition. Here 4 different conditions exist.

In the no-conflict condition, a stimulus only presents one piece of information, the relevant one. In Fig 3 the stimuli in the no-conflict condition provide no information relevant to each of the remaining 3 tasks.

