## 2. Hypotheses (required)

2.1. Task switching cost
2.1.1. Following a switch of the task, the reaction time on said trial is higher than the average reaction time on trials of the same task where previously no switch occurred.2.1.2. Following a switch of the task, accuracy on said trial is lower than the average accuracy on trials of the same task where previously no switch occurred.2.2. Similarity Effects: Task Switching costs (hypothesis 1; Reaction time and accuracy), are more pronounced if the switch is between two more dissimilar tasks.2.3. Conflict Effects:
2.3.1. An incongruent stimulus will result in a higher reaction time regardless of whether the trial is a switch trial or a repetition trial.2.3.2. An incongruent stimulus will result in a lower accuracy regardless of whether the trial is a switch trial or a repetition trial.2.4. Mental Fatigue:
2.4.1. As time on task increases, the reaction times will increase regardless of whether the trials are switch trials or repetition trials.2.4.2. As time on task increases, error likelihood will increase regardless of whether the trials are switch trials or repetition trials.2.4.3. As time on task increases, Task Switching costs (hypothesis 1) will increase

Design Plan

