## 15. Data exclusion (optional)

To detect and reject outliers two steps will be implied. First trials with reaction times of above 5 seconds will be rejected and counted as misses. In addition, an outlier detection will be performed based on the interquartile range criterion. This will be done for trials grouped by condition.

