## 17. Exploratory analysis (optional)

We expect that responses on subjective questionnaires as well as demographics may be valuable covariates partially explaining the variations in reaction time and accuracy, within an exploratory analysis we, therefore, aim to investigate such possible links.

A frequently reported effect during behavioral tasks is the so-called rebound effect, of a lower performance following an error. This may also be analyzed in the context of explaining task-switching costs.

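### Trials that follow an error stay in the main models with switch status coded from the cued task; a prespecified rule for them would protect the test that switch costs grow with time on task

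*Protocol article*

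**What the plan says.** Study design (section 7, Task-Switching Conditions) gives the coding rule: "Each trial (n) is classified into one of the three Task-Switching Conditions depending on the task in trial n-1". It continues: "If the task remains the same, the trial is a repeat trial". A change of task is an internal or external switch according to domain. Nothing makes the code depend on the answer given on n-1.

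Data exclusion (section 15) has two steps. The first is "First trials with reaction times of above 5 seconds will be rejected and counted as misses". The second is "In addition, an outlier detection will be performed based on the interquartile range criterion", applied by condition. Missing data (section 16) removes incomplete trials. None of these concerns the trial after an error.

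The Analysis Plan lists trial type, conflict and conflict congruency as predictors in both models, with response added for reaction time, time on task as covariate, and participant and task effects. Previous-trial accuracy is not listed.

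Exploratory analysis (section 17) mentions a rebound effect "of a lower performance following an error. This may also be analyzed in the context of explaining task-switching costs".

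Hypothesis 2.4.2 reads "As time on task increases, error likelihood will increase regardless of whether the trials are switch trials or repetition trials", and 2.4.3 reads "As time on task increases, Task Switching costs (hypothesis 1) will increase".

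**The concern.** The Introduction attributes switch costs, on one of its two theories, to interference from the task set active on the previous trial. That is the set the participant used. After a wrong-task response it is not the cued one: a coded repeat is then a real switch, and a coded switch may be a real repeat.

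The design makes such responses possible. Four tasks share two keys, and irrelevant cues can point to the opposite key. The note closing the Introduction and the Congruency Conditions text both accept that an irrelevant cue may drive a response. Later training blocks drop feedback to match the experimental conditions, so nothing external corrects the participant.

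Mixing real switches into coded repeats, and the reverse, shrinks the estimated cost. If errors become more frequent during the session, the shrinkage grows with time on task. That opposes the interaction that tests hypothesis 2.4.3.

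**Working it through.** The protocol has no figure of its own to reproduce here: it gives no error rate and no breakdown of error types. Both are assumed below and varied.

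**Inputs.** From the protocol: four tasks in two domains; 5 blocks of 336 trials, so 5 x 336 = 1680 per participant. Assumed: e, the error rate on n-1; w, the share of errors in which another task was performed; the wrong task equally likely to be any of the other three; e and w the same before coded repeats and coded switches.

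**Mean switch cost.** Let C be the true cost.
- Coded repeats: a fraction ew are real switches, so their mean rises by ewC.
- Coded switches: a fraction ew follow a wrong-task response, and in 1/3 of these the task performed was the current one. Their mean falls by ewC/3.
- Observed cost = C x (1 - ew - ew/3) = C x (1 - (4/3)ew).

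| Bias toward zero | e = 5% | e = 10% |
|---|---|---|
| w = 0 | 0 | 0 |
| w = 0.25 | 1.7% | 3.3% |
| w = 0.5 | 3.3% | 6.7% |

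For example, (4/3) x 0.10 x 0.5 = 0.067.

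**Growth with time on task (2.4.3).** Observed growth factor = true factor x (1 - (4/3)w x late e) / (1 - (4/3)w x early e). Let errors rise from 5% to 10% and the true cost grow by 10%:
- w = 0.25: 1.10 x 0.9667/0.9833 = 1.081, seen as 8.1%.
- w = 0.5: 1.10 x 0.9333/0.9667 = 1.062, seen as 6.2%.

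With no true growth and w = 0.5, the factor is 0.966, an apparent fall of 3.4%.

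**Similarity contrast (2.2).** Take e = 10%, w = 0.5, so ew = 0.05, and assumed true costs of 100 ms (internal) and 150 ms (external).
- Wrong tasks equally likely: the 50 ms difference becomes 46.7 ms.
- 60% of wrong-task responses go to the same-domain task: coded repeats rise by 0.05 x (0.6 x 100 + 0.4 x 150) = 6. Internal cost = 95 + 0.05 x 0.4 x 150 - 6 = 92. External cost = 142.5 + 0.05 x (0.6 x 150 + 0.2 x 100) - 6 = 142. The difference stays at 50 ms.
- The same 60% with both true costs at 100 ms: a zero difference becomes +2 ms.

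So neither the size nor the direction is fixed for this contrast.

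**What dropping post-error trials achieves.** On congruent conflict trials the wrong rule still yields the right key, so it goes undetected. Take e = 10% and w = 0.5, with undetected wrong-task responses as common as detected ones (5% of trials each). The total bias is (4/3) x 0.10 = 13%. After dropping the 10% of trials that follow errors it is (4/3) x 0.05/0.90 = 7%. Exclusion removes only part.

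**Cost in data.** At e = 5%, 10% and 15%, about 84, 168 and 252 of 1680 trials are lost. If standard errors scale with the trial count, they widen by 1/sqrt(0.95) = 1.03 to 1/sqrt(0.85) = 1.08. First-of-block trials are 5 of 1680, or 0.3%.

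**The case against.** The strongest reply is that nothing here is stated wrongly. Hypotheses 2.1.1 and 2.1.2 speak of trials following a switch of task, and coding by cued task implements exactly that. That stands: the coding is not an error. Trial cleaning is also often left to a fuller analysis plan, which is not shown. That carries less weight here, because the article does set out its exclusion steps and model terms, and assigns the post-error effect to exploratory work.

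The mechanism is also limited. No-conflict trials carry no information for another task. If the four conflict conditions are equally frequent and half the conflict trials are congruent, detectable wrong-task errors can arise on only 3/4 x 1/2 = 3/8 of trials. A reader might take w = 1, under which the bias doubles to 7-13% at e = 5-10%. That would require every error to be a wrong-task response, which nothing in the protocol supports. Nor does the protocol say that such errors are typical.

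The bias in the mean cost is toward zero, so under this model it cannot create a switch cost or a growth in it. The increase over time presupposes 2.4.2, itself untested. All of this bears on size. It does not remove the exposure of 2.4.3 under the protocol's own prediction.

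Exclusion has its own fault: it conditions on performance, unbalances a balanced design, and removes runs of consecutive errors from the accuracy model. This is why the all-trials result should be kept alongside.

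**Conclusion.** This is a cheap improvement to the plan, not a defect that invalidates an analysis. As written, trials after errors enter the confirmatory models under cue-based codes. If some errors are wrong-task responses, the mean switch cost is understated by about (4/3)ew: 3-7% at e = 5-10% and w = 0.5, and nothing at w = 0. Both e and w are assumptions.

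A reader might infer that the basic switch cost is in doubt. It is not: a few percent matters little against the effect sizes of 0.84 to 1.81 (f-squared) on which section 11 relies. A reader might also infer that the similarity contrast is systematically blurred; its bias depends on which wrong task is performed. A claim that post-error slowing inflates the overall time-on-task slope (2.4.1) would need a slowing figure that the protocol does not give.

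The exposed test is 2.4.3. Under errors rising from 5% to 10% and w = 0.5, a true 10% growth would show as about 6%.

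**What to change.** In Data exclusion (section 15), prespecify that the main reaction-time and accuracy models exclude trials following an error, and the first trial of each block, which has no n-1. Alternatively, keep the post-error trials and add previous-trial accuracy with its interaction with trial type. Report the all-trials analysis as a sensitivity check.

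Add a second sensitivity analysis limited to trials whose n-1 was an incongruent conflict trial answered correctly, since wrong-task responses on congruent trials cannot be seen. With the 3/8 share above, this uses at most about 630 of 1680 trials, so it suits a check and not the main analysis. The Introduction's closing note says irrelevant cues are always incongruent, while Congruency Conditions describes a half-and-half split. These should be reconciled, because the split decides how much goes undetected.

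The argument gives no reason to drop trials that follow a response slower than 5 seconds: slowness does not imply that another task was performed. The rebound effect itself can stay in section 17.

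The cost is a short prespecified rule, a loss of trials roughly equal to the error rate (5-15%, about 3-8% wider standard errors), and more trials lost late in the session if errors rise.

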**Fig 3 pone.0279021.g003:**
[figure not shown]
Examples of the different congruency conditions.

The internal conflict condition adds a piece of information that would indicate the opposite response in the other task of the same domain. In the example, the 3 is the relevant number, due to its position, as the participant is indicated to perform the Even/ Odd task (which is always based on the second number), but the other stimulus (, the 2) would require the participant to respond with the other response if the task were the Low/High task (the task for which, the first number is relevant).

The external conflict condition is similar, with the only difference being, that the non-relevant task is not from the same domain, but is one (and always only one) of the tasks from the other domain.

The final condition, internal & external conflict combines the two other conflict conditions, where both the other internal task and one (and always only one) of the external task, bias the participant towards an incorrect response.

In order to avoid participants using task-irrelevant cues as a strategy to increase performance (Logan & Zbrodoff, 1979) half of the trials will include congruent task-irrelevant stimuli and half of the trials will include task-irrelevant incongruent stimuli. Task irrelevant stimuli will always all be either congruent or incongruent. The downside of this is, that it becomes impossible, during trials with congruent task-irrelevant stimuli, to determine whether a correct or incorrect answer occurred due to the task-relevant or task-irrelevant stimulus. For any analysis that requires this, only the incongruent task-relevant trials may be used.

The locations of the relevant stimuli for the numeric tasks were chosen to be Low/High on the left and Even/Odd on the right for the following reason. Should participants perceive two single digits not as e.g. seven and one but as seventy-one, this would not change the responses. As the Even/Odd relevant number is located (right, or for this discussion 2.) it determines whether a number is odd or even, independent from the number to the left of it (that is to say, both 1 and 71 are odd numbers). In a similar way, the size of the first number is somewhat independent of the second number (7 is larger than 5, but 71 is also larger than any number in the fifties).

Trial Setup:

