## 12. Manipulated variables (optional)

Stimuli:

**Numeric Value:** The value of the stimuli that are presented is manipulated. Participants with see combinations of the numbers 1,2,3,4,6,7,8 and 9 and symbols %, &, € and $.

**Color:** The stimuli color is manipulated to either be hot (red/orange hues), cold (blue/ green hues) or neutral (grey hues).

**Pattern:** The pattern of the stimuli is manipulated and can either show a horizontally oriented pattern, a vertically oriented pattern or a random pattern.

**Task:** The task that participants have to complete given the stimuli can be adapted as can be seen in Figs 1 and 2 the four tasks are Low/High, Even/Odd, Cold/Hot, Vertical/Horizontal.

**Conflict**: Depending on what stimuli are presented together the experiment manipulates the degree of conflict. See Fig 3.

**Conflict Congruency:** The conflict stimuli can be either congruent or incongruent with the task relevant stimulus.

Covariate:

Time on task (TOT), how long the participant has been performing the task, will be incorporated into the analysis as a key covariate indicator of mental fatigue.

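### Numeric no-conflict trials are not free of competing information: every digit has both a magnitude and a parity on the same two keys, and no model term represents this

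*Protocol article*

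**What the plan says.** The Congruency Conditions part of section 7 defines the baseline of the four-level Conflict factor: "In the no-conflict condition, a stimulus only presents one piece of information, the relevant one". It adds, for its figure: "In Fig 3 the stimuli in the no-conflict condition provide no information relevant to each of the remaining 3 tasks".

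The two numeric tasks are described in the same section. In one, participants "judge, whether a single number is higher or lower than 5"; in the other they "decide if a stimulus (again a single number, but located spatially different) is even or odd". The left position is relevant for Low/High and the right for Even/Odd. All four tasks are answered "using either the S or the L key on a keyboard". Section 12 gives the digit set as "combinations of the numbers 1,2,3,4,6,7,8 and 9", together with four symbols, a neutral grey for colour and a random pattern for orientation.

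Section 7 makes irrelevant cues congruent on half of the trials. It accepts that on those trials one cannot tell which cue produced the answer, and sets this safeguard: "For any analysis that requires this, only the incongruent task-relevant trials may be used".

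The Analysis Plan models reaction time on trial type, conflict level, congruency and response, and accuracy on the first three. Time on task is a covariate, and participant and task are dummy coded.

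**The concern.** The visual tasks can meet the definition of no conflict, because colour and pattern each have a neutral level. The numeric tasks cannot: no permitted digit is neutral on magnitude or on parity. Position tells the participant which digit to use, but it does not take the second attribute out of that digit.

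Three things are at stake:

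- **Baseline.** The reference level of Conflict does not mean the same in the two domains.
- **Similarity contrast.** Hypothesis 2.2 compares external with internal switches. After an internal numeric switch the relevant digit always carries the attribute of the task just left. After an external switch at the no-conflict level that attribute is absent.
- **Accuracy.** On an incongruent numeric trial, a participant who applies the wrong numeric rule to the relevant digit still presses the correct key if the digit is a same-key one. Restricting to incongruent trials therefore does not fully identify the cue used.

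**Working it through.** **The plan's own count.** Section 7: 4 tasks x 3 switching x 4 congruency x 2 responses = 96 conditions, and 3 x 4 = 12 main conditions. Both reproduce.

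**Digits under the two rules.** There are 2 x 2 = 4 key mappings, but only the pairing of magnitude with parity matters.

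| Pairing | Opposite-key digits | Same-key digits |
|---|---|---|
| low and even share a key | 1, 3, 6, 8 | 2, 4, 7, 9 |
| low and odd share a key | 2, 4, 7, 9 | 1, 3, 6, 8 |

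The opposite-key share is 4/8 = 50% either way. Each task-by-response combination has two digits of each kind; an odd response, for example, uses 1, 3, 7 or 9.

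**The protocol's own example.** The task is Even/Odd and the relevant digit is 3. The neighbouring 2 counts as internal conflict because low calls for the other key. But 3 is itself low. With a symbol in place of the 2, the trial would be labelled no-conflict while the 3 still carried the same opposing attribute.

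**Trials affected per participant** (5 x 336 = 1680, section 10; even use of tasks and digits assumed). The split over conflict levels is not stated, so two layouts are shown.

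- Four equal conflict levels: 1680/4 = 420 no-conflict, 210 numeric, about 105 opposite-key.
- Seven equal levels (none, plus 3 conflict levels x 2 congruency): 4 x 3 x 7 x 2 = 168 cells; 1680/7 = 240 no-conflict, 120 numeric, about 60 opposite-key. This layout is a reconstruction. It fits the block length (336/168 = 2), whereas 336/96 = 3.5.

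**Conflict contrast** (internal incongruent minus none, true effect scaled to 1).

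- Additive effects, balanced digits: numeric (1 + 0.5) - 0.5 = 1; visual 1; pooled 1.00. No bias.
- Any single incongruent cue produces the full effect: numeric 1 - 0.5 = 0.5; visual 1; pooled (0.5 + 1)/2 = 0.75.

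**Similarity contrast** (external minus internal, at the no-conflict level). Let an opposite-key digit cost x ms more after an internal than after an external switch, and let a same-key digit save f times x. Half of the trials are numeric and half of the digits opposite-key:

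shift = -0.5 x (0.5x - 0.5fx) = -0.25x(1 - f)

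| assumed x (ms) | f = 0 | f = 0.5 | f = 1 |
|---|---|---|---|
| 5 | -1.25 | -0.625 | 0 |
| 10 | -2.5 | -1.25 | 0 |
| 20 | -5 | -2.5 | 0 |
| 40 | -10 | -5 | 0 |

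The documents give no value for x or f.

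**The case against.** The best defence is that conflict is defined by location. On a no-conflict Even/Odd trial the Low/High position can hold a symbol, so nothing stands where a Low/High decision is made. On that operational definition section 7 is coherent, and the overlap matters only if participants apply a rule to the digit in the wrong place. This may well weaken the effect, but it does not remove it. The internal-conflict manipulation itself supposes that irrelevant numeric attributes can bias the response.

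Other points stand in part:

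- The overlap is present at every conflict level, section 8 promises a balanced design, and the task dummies absorb a constant difference between tasks. They do not absorb an effect that differs by trial type within the numeric tasks.
- The safeguard on accuracy concerns irrelevant stimuli and applies only to analyses that need it; no listed analysis sets out to identify the cue used.
- Numeric value is a manipulated variable, so digit type can be derived if the stimulus list is kept.

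A reader might infer that the conflict contrasts are contaminated throughout, that hypothesis 2.2 is necessarily pulled towards zero, or that a definite loss of power follows. The documents support none of these. The first needs non-additivity or imbalance. The second needs interference to exceed facilitation, and section 1 sets the interference view beside a competing account without choosing. The third would need an effect size, variances and an overlap cost that the documents do not give.

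**Conclusion.** The statement that no-conflict stimuli carry only the relevant information is wrong for the numeric tasks. That follows from the digit set and the shared keys, without further assumption. With even digit use, half of numeric no-conflict trials (about 60 to 105 per participant) hold an opposite-key attribute, and the models as listed cannot represent it.

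The consequences are conditional. Conflict-level contrasts are unbiased if effects are additive and digits balanced. The similarity contrast may shift by about -1 to -10 ms for an assumed x of 5 to 40 ms without facilitation, and by 0 with equal facilitation. Any net cost under the interference view would work against hypothesis 2.2, so it would not create the expected result; it could, however, make a null or small result hard to read.

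**What to change.** 1. Constrain the trial list so that same-key and opposite-key digits are equally frequent within each numeric cell. With 168 cells and two trials per cell per block, one of each fits; under another layout, balance as closely as possible over the whole session.
2. Derive within-digit congruency (same-key, opposite-key, not applicable for visual tasks) and enter it with its trial-type interaction in both models. Its not-applicable level coincides with the visual task dummies, so one main-effect term is redundant; the interaction terms remain estimable.
3. Report the external-minus-internal contrast by domain as well as pooled. This is needed beside item 2 because there is no neutral digit: the model estimates the extra opposite-minus-same difference after internal switches, D = x(1 + f), not the net shift. For f between 0 and 1 the shift then lies between -0.25D and 0.
4. Call the numeric level 'no added cue'.
5. Restrict any accuracy analysis that infers which cue was used in the numeric tasks to opposite-key digits.

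The cost is one list constraint and one derived variable, with no added trials or participants. The price is a few more model terms and lower precision for the by-domain contrasts. Section 9 states that registration precedes data collection, so the list can still be constrained.
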